**Safety outcomes**

The percentage of patients having at least one category of AE, SAE and SUSAR, will be compared by the Fisher’s exact test.

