- Evaluation of resolution of the infection and potential recurrence of infection according to the judgment of the attending physician
- Evaluation of potential adverse events

Visit 10 is on day 10. Procedures of this day include:

- Recording of SOFA score (see APPENDIX II); available blood cell count, biochemistry, coagulation times, urine output, blood gases, available radiological findings, clinically relevant microbiology and antimicrobial susceptibility testing, administered antimicrobials, other administered drugs and need for source infection control either by percutaneous interventions or by any operation.
- Survival status
- Evaluation of resolution of the infection and potential recurrence of infection according to the attending physician
- Sampling of 33 ml of venous blood; 9ml is collected into one pyrogen-free tube; and 24ml is collected into EDTA-coated tubes
- Evaluation of potential adverse events

Visits 11-28 are on days 11-28 respectively. They include

- Recording of SOFA score if available
- Administered antimicrobials, other administered drugs and need for source infection control either by percutaneous interventions or by any operation.
- Survival status
- Evaluation of resolution of the infection and potential infection recurrence according to the judgment of the attending physician
- Evaluation of potential adverse events

If the patient is discharged before day 28, a phone call will be performed on day 28 to assess survival status, need for new hospitalization or antibiotic therapy and potential adverse events. End-of-life decisions, if any, will be recorded.

Last visit: A phone call follow-up will be done on day 90 to assess survival status. If available, data concerning any new hospitalization, or antibiotic cure and potential adverse events will be collected during that phone call. Moreover, a self or proxy-assessment of health-related quality of life will be performed through the EQ-5D-3L^™^ questionnaire on the same visit (see APPENDIX IV) ^18^.

All information will be recorded on a specific paper Case Report Form (CRF).

The procedure to follow at each study visit is shown in APPENDIX V.

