**POWER CALCULATION**

This is done for the primary study endpoint. We are planning a study of independent cases and controls with 1 control per case. Prior data indicate that the mortality among placebo-treated patients with sepsis and respiratory dysfunction was 55% and that this was decreased to 30%^11^. We need to study 55 subjects into each group to be able to reject the null hypothesis that the failure rates for both groups are equal with probability (power) 0.8. The Type I error probability associated with this test of this null hypothesis is 0.10. We will use a continuity-corrected chi-squared statistic or Fisher’s exact test to evaluate this null hypothesis.

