**ADVERSE EVENTS**

Adverse events (AEs) and Serious Adverse Events (SAEs) will be collected from baseline until the last patient’s last evaluation. An adverse event is any undesirable medical occurrence in a subject receiving a pharmaceutical product and which does not necessarily have a causal link with this treatment. The adverse event may be a sign, a symptom, or an abnormal laboratory finding.

An adverse reaction is any undesirable and unintended reaction due to investigational medicine product administration (or intervention), related with any dose administrated. If an adverse event/ reaction meets any of the following criteria, it is considered as a *Serious Adverse Event/ Reaction* (SAE):

- Death
- Life-threatening situation The subject was at risk of death at the time of the adverse event/ experience. It does not refer to the hypothetical risk of death if the AE/ adverse reaction were more severe or were to progress.
- Hospitalization or prolongation of existing hospitalization
- Persistent or significant disability/ incapacity Any AE having an outcome that is associated with a substantial disruption of the ability to carry out normal life functions, including the ability to work. This is not intended to include transient interruption of daily activities.
- Congenital anomaly/ birth defects Any structural abnormality in subject’s offspring that occurs after intrauterine exposure to treatment.
- Important medical events/ experiences that may not result in death, be life-threatening, or require hospitalization, may be considered as SAE when, based upon appropriate medical judgment, they may jeopardize the subject and may require medical or surgical intervention to prevent one of the outcomes listed above, i.e. death, a life-threatening adverse event/experience, inpatient hospitalization or prolongation of existing hospitalization, a persistent or significant disability/ incapacity, or a congenital abnormality/ birth defect. Examples of such medical events/ experiences include allergic bronchospasm requiring intensive treatment in an emergency room or at home, blood dyscrasias or convulsions that do not result in inpatient hospitalization, or the development of drug dependency or drug abuse.
- Spontaneous and elective abortions experienced by study subject

*A non-serious adverse event* is one that does not meet the previous definition of a SAE. The severity of the non-serious adverse events will be graded using the following definitions:

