**Safety outcomes**

- Adverse events (AEs)
- Serious adverse events (SAEs)
- Suspected unexpected serious adverse reactions (SUSARs)

Patients are followed-up daily until day 28 or hospital discharge (whatever comes first). In case of earlier discharge, the primary outcome, is assessed by phone call at day 28. 90-day mortality and quality of life by the EuroQol**^®^** 5-dimension 3-level (EQ-5D-3L) questionnaire (1), in case of discharge, are also assessed by phone call with the patient or their caregiver. Safety outomes are captured daily until day 28 or discharge (whichever comes first) and as patient or provider-reported events until day 90. All other secondary outcomes are assessed until day 28 or discharge.

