**Analyses for secondary outcomes**

The effect of the study arm on secondary outcomes will be compared with the Pearson chi-square test, or the two-sided Fisher’s exact test for 90-day mortality, early sepsis response and sepsis resolution, as well as new sepsis incidence. Clinical secondary outcomes will be evaluated on an ITT basis.

- Regarding 90-day mortality, the following subgroup analyses are planned (for all subpopulations identified): per country; per ward of enrollment (ICU or general ward); per protocol (according to whether the study intervention was complete -all 4 doses received); per presence of septic shock (already present in the protocol); per highest SOFA score (defined as higher or lower than the upper SOFA quartile of the population); per presence of ARDS; per initial infectious site; per adequacy of empirical antimicrobial treatment; and per Gram-negative vs non-Gram negative pathogen, among infections with identified pathogens. Interactions between subgroups and arm of treatment were assessed with Breslow-Day test and confirmed with logistic regression for the primary outcome.
- The time to new sepsis incidence will be compared only for patients experiencing a new sepsis episode both by the Mann-Whitney test, and as Cox-regression analysis of the treatment effect on the time to new sepsis episode, with death as competing event.
- Cell populations and monocytic HLA-DR variables will be assessed using Student’s t-test (for variables following a normal distribution), Mann-Whitney U (for variables following a skewed distribution), as appropriate. Overtime changes will be assessed by the k-related samples non-parametric Friedman test, separately per study arm, and the mixed ANOVA test with time and study arm as within-subject and between-subject factors respectively.
- Transcriptomic data wil be illustrated by Volcano plots for differential expression of genes among study groups, while gene set enrichement analysis will also be performed to identify pathways of transcriptomic changes among study groups. Any need for additional (post-hoc) analyses will be re-evaluated. Functionality of differentially expressed transcripts will be assessed by the ENCODE project.

Raw sequence data and count data will be uploaded on National Center for Biotechnology Information (NCBI) gene expression omnibus (GEO), to be publicly available.

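### AE, SAE and SUSAR percentages are compared by Fisher's test with no time window and no account of follow-up, although planned mortality is 55% vs 30% and capture thins out after discharge

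*Supplement*

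**What the plan says.** **Analysis.** The SAP section on the analysis of safety outcomes reads: "The percentage of patients having at least one category of AE, SAE and SUSAR, will be compared", by Fisher's exact test. It gives no window, person-time, time-to-event method or rule for patients who die.

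**Capture.** The SAP's earlier Safety outcomes section states: "Safety outomes are captured daily until day 28 or discharge (whichever comes first) and as patient or provider-reported events until day 90". In protocol version 2, Study visits, a patient who leaves hospital early is still followed up: "a phone call will be performed on day 28 to assess survival status, need for new hospitalization or antibiotic therapy and potential adverse events". At the day-90 call, if data are available, "antibiotic cure and potential adverse events will be collected during that phone call". The protocol's Adverse events section says that AEs and SAEs "will be collected from baseline until the last patient’s last evaluation". Study visits also lists AE evaluation on each of visits 11 to 28, but the schedule in Appendix V marks AE monitoring for visits 1 to 10 only.

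**Deaths.** The Adverse events section puts death first among the SAE criteria. It then says that events resulting from sepsis or infection, deaths included, are not recorded as AEs or SAEs.

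**Expected mortality.** The protocol's Power calculation says that mortality among "placebo-treated patients with sepsis and respiratory dysfunction was 55% and that this was decreased to 30" per cent.

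**Elsewhere in the SAP.** Under secondary outcomes, Cox regression is planned "on the time to new sepsis episode, with death as competing event". The incidence of new sepsis is compared by a chi-square or Fisher test.

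**The concern.** A percentage with at least one event depends on how long each patient is watched. Someone who dies of sepsis on day 3 with no other event counts as free of AEs and SAEs, exactly like a 28-day survivor with no event. If mortality differs as planned, the surviving arm has more days in which to have an AE, and a Fisher test cannot separate a difference in risk from a difference in time at risk. If instead the drug shortened survival, early deaths would remove patients from capture and could mask toxicity. Discharge adds a second imbalance, because how closely patients are watched then depends on an outcome that may itself differ by arm.

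At stake is how the safety table is read. A difference between arms, or the absence of one, could partly reflect survival and discharge.

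**Working it through.** **1. The plan's own figure.** With p1 = 0.55, p2 = 0.30, mean 0.425, two-sided alpha 0.10 and power 0.80:

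n = [1.645·√(2·0.425·0.575) + 0.842·√(0.55·0.45 + 0.30·0.70)]² / 0.25² = 47.3.

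The continuity correction is (n/4)·[1 + √(1 + 4/(0.25·n))]² = 55.0. The stated 55 per arm is reproduced, so 55% and 30% are the operative mortality assumptions.

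**2. Death hazards (assumed constant to day 28).** Placebo: −ln(0.45)/28 = 0.0285 per day. Clarithromycin: −ln(0.70)/28 = 0.0127 per day.

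**3. Observation time to day T, ignoring discharge.** The mean is (1 − exp(−hT))/h.

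| Window | Placebo (days) | Clarithromycin (days) | Ratio |
|---|---|---|---|
| Day 5 | 4.66 | 4.84 | 1.04 |
| Day 10 | 8.7 | 9.4 | 1.08 |
| Day 28 | 19.3 | 23.6 | 1.22 |

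**4. Patients with at least one AE, same AE hazard l in both arms.** P = l/(l+h)·[1 − exp(−(l+h)T)]. The documents give no AE rate, so l is an assumption shown as a range. The last column is the chance that Fisher's test (two-sided 0.05, 55 per arm) rejects at day 28.

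| l per day | Day 28, placebo vs clarithromycin | Gap, day 28 | Gap, day 10 | Gap, day 5 | Fisher rejects |
|---|---|---|---|---|---|
| 0.01 | 17.1% vs 20.7% | 3.6 | 0.6 | 0.2 | 4% |
| 0.02 | 30.6% vs 36.7% | 6.0 | 1.2 | 0.3 | 7% |
| 0.05 | 56.6% vs 65.9% | 9.3 | 2.5 | 0.8 | 12% |
| 0.10 | 75.7% vs 84.9% | 9.2 | 3.7 | 1.3 | 16% |

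Gaps are in percentage points. With equal true percentages, Fisher's test rejects about 3% of the time here.

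Since the SAP names no window, the longest reading is day 90. Assuming no deaths after day 28 and unchanged capture, mean observation is 47.2 vs 67.0 days (ratio 1.42), and the gap over the same AE rates is 11 to 17 points.

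**5. Can the direction change?** Yes, in two ways.
- *Discharge.* For daily capture only, mean time is (1 − exp(−(h+d)·28))/(h+d), with d an assumed discharge hazard. With d = 0.01 on placebo and 0.03 on clarithromycin it is 17.1 vs 16.3 days, so the order reverses. Break-even is an excess discharge hazard of 0.0285 − 0.0127 = 0.0158 per day.
- *Deaths as SAEs.* In the extreme case that every death counted, the SAE percentage is 1 − exp(−(l+h)·28). At l = 0.01 that is 66% on placebo vs 47% on clarithromycin. The protocol exempts sepsis deaths, so the real pull is smaller, but it is opposite in sign.

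**6. Which alternatives help?**
- *Cumulative incidence with death competing.* The formula in step 4 is already that quantity. Without discharge censoring it equals the crude percentage and leaves the gap as it is.
- *One patient-day rate to day 28.* Suppose an AE hazard of 0.05 per day in both arms on days 0 to 5 only. Crude percentages are nearly equal, 20.7% vs 21.5%. The rates are 100·0.05·4.66/19.29 = 1.21 and 100·0.05·4.84/23.55 = 1.03 per 100 patient-days. That ratio of 0.85 in favour of clarithromycin comes only from the longer denominator. Splitting the period avoids this.

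**The case against.** The percentage of patients with at least one AE under actual follow-up is a conventional descriptive summary, and at 55 per arm the day-28 gap is modest beside its noise: the standard error of the difference is 7.5 to 9.2 points over these AE rates. Study drug is given for four days, and the protocol limits the time relationship to treatment plus five half-lives. For events that early the gap is small. This stands. It makes the point one of interpretation and size, and it supports an early window as the main comparison.

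A reader might infer that AE capture stops at discharge. The documents do not support this: only daily capture stops, with reported events continuing to day 90 and calls on days 28 and 90 that ask about AEs. Death does end capture.

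A reader might also infer that safety has been singled out, because death is a competing event for new sepsis. That method applies to the time to new sepsis; its incidence gets the same crude test as safety. The contrast is weak support.

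The objection does not remove the core problem. The safety analysis has no window, the documents disagree on the capture period, and the planned mortality difference makes observation time unequal.

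**Conclusion.** The point holds in a limited form. The planned test compares percentages over an undefined period, although on the plan's own mortality figures the arms are observed for unequal times. With constant death hazards, an equal AE hazard of 0.01 to 0.10 per day and no discharge, the better-surviving arm shows about 4 to 9 points more patients with an AE by day 28. Fisher's test then rejects in 4% to 16% of trials, against about 3% with equal percentages. By day 5 the gap is 0.2 to 1.3 points.

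Two stronger readings go too far. One is that clarithromycin will look less safe if it works: the direction depends on discharge timing and on non-sepsis deaths counted as SAEs, neither of which the documents quantify. The other is that the safety comparison is uninterpretable: a gap of this size under assumed AE rates does not show that, and early events are little affected.

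**What to change.** In the SAP section on the analysis of safety outcomes:

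1. Make the main Fisher comparison the percentage of patients with an AE, SAE or SUSAR from first dose to day 5, a window common to both arms.
2. For the later period, report the crude percentages beside follow-up time per arm (median and total patient-days, with numbers dead and discharged).
3. Add AE and SAE rates per 100 patient-days, or a cause-specific hazard, separately for the early window and for days 6 to 28. Count events and days on the same basis, and list events reported after discharge separately.
4. If cumulative incidence with death as a competing event is shown, label it descriptive; it does not correct for unequal survival.
5. Reconcile the AE capture period across the SAP's Safety outcomes section and the protocol's Study visits, Adverse events and Appendix V. State how deaths enter the SAE count, given the SAE criteria and the sepsis exemption.

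The cost is a paragraph of SAP text, some programming, and two or three safety summaries where there is now one. No new data are needed, since survival and AEs are assessed at the inpatient visits and follow-up runs to discharge.

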Clarithromycin as adjunctive treatment to standard antibiotic therapy has been used by our group in two previous large-scale multi-center RCTs conducted in Greece after approval from the Greek regulatory authorities. The first RCT studied 200 patients with sepsis due to VAP and it was conducted between 2004 and 2005 ( [www.clinicaltrials.gov](http://www.clinicaltrials.gov) NCT00297674). Identified pathogens mainly included gram-negative bacteria i.e. *Acinetobacter baumanii* and *Pseudomonas aeruginosa* that do not belong to the usual antimicrobial spectrum of macrolides. Although 28-day mortality in both arms was similar, patients assigned to the clarithromycin arm experienced earlier weaning from mechanical ventilation and more rapid resolution of VAP, compared to the placebo arm. In the subgroup of patients with septic shock and multiple organ dysfunction syndrome (MODS), probability of sepsis-related death was significantly lower (OR 3.78 vs 19; *p* = 0.043). Serious adverse events (SAEs) occurred in 3 (3%) clarithromycin-treated patients, with no clear causative link with the study drug in 2 out of 3 cases^9^. Furthermore, hospitalization costs associated with clarithromycin use were significantly reduced (by 7000 euros/ patient that remained alive) compared to the placebo arm^10^.

The second multi-center RCT compared the efficacy of clarithromycin versus placebo added to standard antibiotic therapy in patients with gram-negative sepsis caused by acute pyelonephritis, intra-abdominal infections and primary gram-negative bacteremia; 600 patients were included between 2007 and 2011 ([www.clincialtrials.gov](http://www.clincialtrials.gov) NCT01223690). Overall mortality at 28 days in both arms did not differ, but probability of death due to septic shock and MODS was shown once more lower in the clarithromycin-treated group (OR 3.58 vs 6.21; p = 0.036). Interestingly, survival benefit from clarithromycin was even greater in those patients suffering from adult respiratory distress syndrome (ARDS). SAEs were described in 2 (0.7%) patients treated with clarithromycin, while its use was associated with saving of a median of 1000 euros/ hospitalized patient^11^. No QT space prolongation or any arrhythmia was observed in both aforementioned trials.

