**Randomization and bliniding**

Patients are assigned to clarithromycin or placebo, following a random allocation sequence, with a 1:1 design and by block sizes of 10, stratified per study site. The allocation sequence was generated by an independent statistician prior to the study start and delivered within sealed individual envelopes, labeled per study participant code, to each study site. The envelope is unsealed by the study pharmacist (the only unblinded investigator), to prepare the study drug. All other parties involved (investigators, patients, healthcare providers) are blinded to the study arm.

Study intervention consists in either 1gr of clarithromycin or 20 ml of water for injection (placebo), administered once daily as a ready-to use intravenous solution of 250 ml D/W 5%. The intervention is administered for 4 consecutive days, as soon as possible after enrollment. There is no specific time window from enrollment to study drug administration, which is required to be as soon as logistically possible.

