**Sample size calculation**

This is done for the primary endpoint. Based on previous studies, we anticipated a 25% reduction of mortality among patients with sepsis and respiratory dysfunction, treated with clarithromycin. To detect this difference with a type-I error of 0.10 and a type-II error of 0.8 and anticipating a 10% loss to follow-up, 55 patients need to be enrolled in each study arm.

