**General principles**

- This analysis plan and the primary manuscript will include clinical data up to 90 days, transcriptomic and cell population (by flow cytometry) analyses; the entire cost-effectiveness analysis, cytokine analysis (including serum cytokine concentrations and cytokine production from supernatants of ex-vivo stimulated peripheral blood mononuclear cells-PBMCs) and microbiome analysis will be reported separately.
- Regarding flow cytometry analysis (including cell population and HLA-DR analysis), only samples from patients enrolled in sites proximal to the central lab (Athens) could be included in the current study.
- Regarding trasncriptomic analysis, only a subset of sample sequencing could be covered by the study funding at the time of the present statistical analysis plan. Thus, it was decided to only include in the primary manuscript samples from the subgroup of patients of extremely high severity (within the highest quartile of baseline SOFA score), to demonstrate differences between death and survival. The entire transcriptomic analysis, combined with metabolome, cytokine and microbiome analysis will be reported separately.
- All p-values will be two-sided and the level of significance will be <0.05.
- No interim analysis is planned.
- Regarding clinical data, cell populations and HLA-DR measurements, no adjustment for multiple comparisons is planned and all secondary outcomes will be viewed as exploratory. For transcriptomic data, statistically significant differences will be defined by Benjamini & Hochberg adjusted probabilities < 0.05 and absolute fold expression ≤−1.5 or ≥1.5.
- Analyses will be conducted primarily by the SPSS statistical software, version 24 (IBM) or later; transcriptomic data twill be analysed in the R statistical framework (Version 3.51, R Core Team 2014. R: A language and environment for statistical computing. R Foundation for Statistical Computing, Vienna, Austria)
- Results will be presented by order of importance, starting with the primary outcome first. Due to the nature of the study, additional exploratory analyses will be performed based on the primary and secondary outcomes, in an effort to identify potential host immune pathways modulated by the study drug.

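### Safety is compared between arms only by Fisher p-values, with no risk difference or interval, so at 55 per arm a sizeable excess of uncommon events would show only as non-significance

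*Supplement*

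**What the plan says.** The SAP section on safety outcomes that follows the secondary analyses has one analysis sentence: "The percentage of patients having at least one category of AE, SAE and SUSAR, will be compared by the Fisher’s exact test". The significance rule comes from the SAP's General principles: "All p-values will be two-sided and the level of significance will be <0.05". The Descriptives section adds that categorical variables are shown as counts and percentages.

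Neither the SAP nor version 2 of the protocol plans a risk difference, risk ratio, confidence interval or upper bound for a safety outcome. For the primary outcome, by contrast, the SAP plans a Cox effect size and an absolute mortality difference with a 95% CI.

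The trial is sized on mortality alone: "55 patients need to be enrolled in each study arm". No detectable difference for harm is stated, and no placebo-arm SAE or SUSAR rate is given. The protocol's Introduction quotes two SAE rates, both from clarithromycin arms of previous trials: "Serious adverse events (SAEs) occurred in 3 (3%) clarithromycin-treated patients" in the first trial, and 2 patients (0.7%) in the second.

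**The concern.** A test alone answers only whether the arms differ detectably. In a trial sized for a 25-point mortality difference, a moderate excess of an uncommon event will often be non-significant even when it is real. The planned output would then be two percentages and a p-value above 0.05, with no prespecified statement of how much excess harm the data still allow. What is at stake is how the harm results are described. The efficacy result is not affected. The authors plan interval estimation for benefit and leave it out for harm, where small counts make it more useful.

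**Working it through.** **Inputs.** 55 per arm (SAP, Sample size calculation); allocation "with a 1:1 design and by block sizes of 10" (SAP, Randomization); Fisher's exact test (SAP, Safety outcomes); two-sided 0.05 (SAP, General principles). The event rates are assumptions, guided only by the 3% and 0.7% in the Introduction.

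**1. The plan's own figure.** The protocol's Power calculation assumes that mortality "was 55% and that this was decreased to 30"%, a type I error of 0.10, and enough patients "to reject the null hypothesis that the failure rates for both groups are equal with probability (power) 0.8". With mean rate 0.425, z = 1.645 and 0.842:

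n = [1.645·√(2·0.425·0.575) + 0.842·√(0.55·0.45 + 0.30·0.70)]² / 0.25² = 47.3, so 48 per arm.

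The continuity correction, (n/4)·[1 + √(1 + 4/(n·0.25))]² with n = 47.3, gives 55.0. The stated 55 is reproduced (reading the SAP's type II error of 0.8 as power). It says nothing about detecting harm.

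**2. SUSARs, k against 0.** Two-sided Fisher p = 2·C(55,k)/C(110,k).
- k = 5: 2·(55·54·53·52·51)/(110·109·108·107·106) = 2·0.0284 = 0.057.
- k = 6: 0.057·(50/105) = 0.027.

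Five treated patients (5/55 = 9.1%) against none is therefore non-significant; six is the first significant count. With 50, 53 or 54 per arm, 5 against 0 still gives p of 0.056 to 0.057.

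**3. Observed tripling of SAEs.** The Newcombe interval combines the Wilson limits (l, u) of each arm, where d = pC − pP:

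lower = d − √[(pC − lC)² + (uP − pP)²]; upper = d + √[(uC − pC)² + (pP − lP)²].

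For 6 against 2: pC = 10.91% (5.10 to 21.83), pP = 3.64% (1.00 to 12.32), d = 7.27. Lower = 7.27 − √(5.81² + 8.68²) = −3.2. Upper = 7.27 + √(10.92² + 2.64²) = +18.5.

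| Clarithromycin vs placebo, of 55 | Placebo rate | Fisher p | Difference, points (95% CI) |
|---|---|---|---|
| 3 vs 1 | 1.8% | 0.62 | +3.6 (−4.9 to +13.2) |
| 6 vs 2 | 3.6% | 0.27 | +7.3 (−3.2 to +18.5) |
| 9 vs 3 | 5.5% | 0.12 | +10.9 (−1.1 to +23.3) |
| 12 vs 4 | 7.3% | 0.056 | +14.5 (+1.2 to +27.8) |
| 15 vs 5 | 9.1% | 0.024 | +18.2 (+3.7 to +32.1) |

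The switch comes between 4/55 and 5/55 on placebo.

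**4. Power for a true tripling.** Power = Σ Bin(a; 55, pC)·Bin(b; 55, pP), summed over all pairs (a, b) that Fisher's test rejects at 0.05.

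| Placebo rate | Clarithromycin rate | Power |
|---|---|---|
| 0.7% | 2.1% | below 1% |
| 3% | 9% | 12% |
| 5% | 15% | 29% |
| 7% | 21% | 46% |
| 10% | 30% | 68% |
| 15% | 45% | 92% |

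**5. Zero events.** For 0/55 the exact upper bound is 1 − 0.05^(1/55) = 5.3% (one-sided 95%) or 1 − 0.025^(1/55) = 6.5% (two-sided 95%).

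**The case against.** Five points can be made for the plan.

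- **The base rate is unknown.** A reader might infer that any tripling of SAEs would be missed, or that the test is close to useless for harm. The figures do not support that: 15 against 5 is significant, a true tripling from 15% has 92% power, and 5% against 25% has 80%. The 3% and 0.7% come from clarithromycin arms, and the severity of this population may push the placebo rate higher. Listing death as an SAE criterion would also push it up; not recording untoward events that result from sepsis or infection pushes it down. This stands, and it limits the point to low base rates.
- **The plan never equates p above 0.05 with equal safety.** A reader might infer that it does. No aim, endpoint or analysis sentence says so. The gap is that no other quantity is prespecified.
- **SUSARs are not judged by the p-value alone.** The protocol's Adverse events section has the sponsor assess expectedness and report confirmed SUSARs within 7 or 15 days. That stands, but case reporting does not estimate the difference between arms.
- **Counts are reported, so a reader can work out the interval.** True. Little information is lost, but the choice of summary is left until after unblinding.
- **At 5 against 0 the Newcombe interval (+0.8 to +19.6) excludes zero while Fisher's p is 0.057.** This partly reflects an exact conservative test set against an approximate interval. The point does not depend on it: at 6 against 2 both methods agree on non-significance, and the interval still shows that an excess of 18.5 points is not ruled out.

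**Conclusion.** The point holds as a modest but real gap in the analysis plan. Safety has a test and no estimate, while mortality has both. At 55 per arm an observed SAE tripling is non-significant when the placebo rate is about 7% or lower, five SUSARs against none is non-significant, and power for a true 3% against 9% is 12%. From a placebo rate of about 9%, an observed tripling is significant. The size depends on the assumed placebo rate, on full enrolment at 55 per arm, and on two-sided 0.05 applying to safety as the General principles say. An interval does not raise the power; it shows how much excess harm remains open. The primary result does not change.

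**What to change.** In the SAP's safety analysis section:

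1. For AEs and for SAEs, report the risk difference (clarithromycin minus placebo) with a 95% CI, for example Newcombe, as the main safety result. Keep any Fisher p-value as supplementary.
2. List SUSARs by arm with exact 95% upper bounds, stating whether these are one-sided or two-sided.
3. State that a non-significant p-value will not be read as evidence of equal safety.

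No acceptance rule on the upper limit is proposed, because the documents define no safety margin.

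The cost is a few sentences in the SAP and one extra column in the safety table, with no new data. The downside is that the safety statement will look less favourable, because wide upper limits become visible.
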